### Perceived function and quality of life

The WOMAC is widely used to evaluate hip and knee osteoarthritis (25). It is a self-administered questionnaire that has been validated in both paper and electronic formats (26). The index consists of 24 items, each with a 5-point Likert scale, and is divided into three subscales: pain (five items), stiffness (two items), and physical function (17 items). Both the English and Chinese versions will be used in this study. The Chinese version of the WOMAC has been validated in previous studies (27, 28). The Musculoskeletal Health Questionnaire (MSK-HQ) contains 14 items and will be used at baseline and at Day 100 to measure pain severity, physical function, and quality of life (29). Pain will also be measured on Days 0, 30, 50, and 100 using the 4-item pain intensity measure (P4), which measures pain intensity over the past 2 days (30).

### Clinical data

Height will be measured using a calibrated stadiometer (SECA, USA) to the nearest 0.1 cm, without shoes. Weight will be measured using a calibrated electronic scale (SECA, USA) to the nearest 0.1 kg. Waist and hip circumferences will be measured over light clothing using a tape measure (Lufkin, USA) to the nearest 0.1 cm. Blood pressure will be measured using an automatic blood pressure monitor (OMRON, Japan) and an appropriately sized cuff while seated after 10 min of rest.

### Dietary and physical activity habits

Dietary habits will be assessed before and after the 100-day intervention using a 7-day food diary. Participants will be instructed to record details of all foods and drinks consumed over the seven days. Diaries will be entered into FoodWorks 10 Professional (Xyris Pty Limited, Australia) for analysis. Self-reported appetite will be measured pre- and post-intervention using a VAS questionnaire. Questions will focus on hunger, fullness, satiety, desire to eat, and prospective consumption (31). The New Zealand Physical Activity Questionnaire Short Form (NZPAQ-SF) (32) will be used to assess the frequency, duration, and intensity of physical activity before and after the 100-day intervention.

### Permitted concomitant care

The consumption of probiotics or herbal medicines is prohibited during this trial due to potential drug interactions. Participants are permitted to use analgesia if needed during the trial. If participants are recommended by their usual healthcare practitioners to start any new medications during the trial, they will be encouraged to discuss this with the PI to determine whether this affects their trial eligibility. Participants will be asked to report all medication use at Days 0, 30, 50, and 100.

### Adverse events

Complications will be reported and described by duration, severity, outcome, treatment, and relation to study treatment or cause. Information on experienced side effects will be collected on Days 30, 50, and 100. Participants are encouraged to discuss any experienced side effects with the PI and their General Practitioner. All serious adverse events will be reported to the ethics committee. An independent data safety monitoring committee consisting of a senior researcher, clinician, and statistician will be formed to review all adverse events and judge their severity and relatedness to the trial using established standards (33). The committee will inform the PI if the adverse events warrant terminating the study. All participants will be immediately informed of the termination. The trial sponsor may also wish to request for early termination of the study.

In the event of injury during this trial, participants are eligible to apply for compensation from the New Zealand Crown entity, Accident Compensation Corporation. It is made clear in the Participant Information Sheet that claims are not automatically accepted.

### Data management

A secure database will be generated, which will be password-protected on a university-provided server and accessible only to research team members. Once written informed consent is obtained from eligible participants, a unique study ID code will be allocated. From this point, all study data and samples will be link-anonymised. All results from study assessments will be entered into password-protected electronic case report forms labeled with participants' unique study ID codes. Paper forms of study data collection will be stored in locked cabinets.

All study data will be collected online through the WeChat social media platform (owned by Tencent Inc.), using an official account and mini-programme specifically designed for this trial by the National Institute for Health Innovation (NIHI), University of Auckland, New Zealand. The decision to use WeChat was based on a prior WeChat-based intervention conducted in Auckland, New Zealand, which targeted a similar population (34, 35). Participants who own a smartphone or tablet and have a WeChat account will have access to the official account and mini-programme of the study. The content, user interface, and user experience design of the official account and the mini-programme were developed based on standardized questionnaires (29–32) and by following the WeChat mini-programme design guidelines (36). All questionnaires will be delivered *via* the WeChat platform. Data will be recorded and stored in the mini-programme. At the end of the study, data will be exported from the mini-programme for analysis. Exported data will be stored safely and password protected. Data in the mini-programme will be purged after 10 years. No routine audits of trial conduct are planned.

### Participant adherence

Links to questionnaires and reminders to complete questionnaires will be provided *via* WeChat. Questionnaires can be completed online at any convenient time, which is expected to promote data completeness. If participants have not completed the required questionnaires within 7 days, a research assistant will phone them and provide an opportunity to complete these questionnaires *via* the telephone. Research assistants will also check responses once questionnaires have been returned and will contact participants to provide any missing data, if necessary. Participants will self-report daily treatment adherence by scanning the unique QR code on the chocolate wrapper using the WeChat mini-programme. Participants will also be asked to retain all chocolate wrappers (opened and unopened) and return them at the final visit (Day 100).

Participants who discontinue treatment early will remain in the trial with ongoing data collection. This includes those who no longer meet the eligibility criteria during the trial due to a change in medication or medical history. If participants withdraw from the study, consent will be sought to use all data collected up to the time of study withdrawal. They will not be replaced.

### Statistical methods

The primary outcomes are change in insulin resistance as defined by HOMA and patient-reported joint pain as measured using WOMAC. A sample size of 150 participants (75 per arm) will provide 90% power at an overall significance level of 5% (two-sided) to detect a standardized effect size of 0.625 on either of the two co-primary outcomes, with the Bonferroni correction (α = 0.025 for each outcome), allowing for 10% loss to follow-up. This effect size is equivalent to a group difference of 1 point on patient-reported joint pain *via* WOMAC and a 0.5-unit difference in change in HOMA, both of which are considered clinically significant. Standard deviation (SD) calculations for pain reduction and change in HOMA were based on previous trials (37, 38).

Statistical analysis will be performed at the end of the trial following an intention-to-treat (ITT) principle, including all randomized participants in the group they were allocated to. No interim analyses are planned during the trial. Trial data will be exported to SAS version 9.4 (SAS Institute Inc., Cary, USA) for analysis. All statistical tests will be two-sided at a 5% significance level. A statistical analysis plan will be prepared a priori by the trial statistician to guide the final data analysis.

Baseline demographics and clinical characteristics of all trial participants will be summarized using descriptive statistics by treatment group. Continuous variables will be presented as mean, SD, median, and interquartile range, as appropriate. Categorical variables will be presented as frequencies and percentages. No formal statistical tests will be conducted at baseline, as previously recommended for parallel-group randomized trials (39).

Outcomes measured at the end of the intervention will be summarized descriptively by the treatment group, together with their baseline measures. Adverse events will be summarized separately. A generalized linear regression model will be used to estimate the effect of the intervention on each outcome, using a link function appropriate to the distribution of the outcome variable. The model will adjust for baseline outcome value and important baseline confounders as pre-specified. Missing data on the primary outcomes will be imputed using multiple imputations in the main ITT analysis and explored in sensitivity analysis under different assumptions to test the robustness of the main trial results. Per-protocol analysis will include participants adherent to the treatment without major protocol deviations. No data imputation will be considered on secondary outcomes. The CONSORT 2010 statement will be used as the guidelines to report the main trial results.

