## Methods/design

### Trial aim and hypothesis

The primary objective of this trial is to determine whether a food product supplemented with green-lipped mussel and fucoidan powder improves joint pain and/or insulin resistance. We hypothesize that the mussel-fucoidan combination will be superior to placebo in reducing patient-reported joint pain and/or improving insulin resistance.

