### Randomization and concealment

Eligible participants will be randomly assigned to receive either the mussel-fucoidan prototype product or the placebo in a 1:1 ratio. The trial biostatistician will prepare the blinded randomization lists using permutated block randomization with variable block sizes. Random pack numbers will be generated in the drug labeling list and pre-packed in identical boxes by Alaron Products Limited. Once a participant has provided informed consent and has been confirmed eligible to be randomized, the database will show the pack number linked to the participant in the allocated group. A research assistant will provide participants with their correct treatment packs, with no information on actual group allocation. Neither the participant nor any research team member will know the treatment product indicated by the randomization. During the trial, the blind may be broken in emergencies, such as when knowledge of the participant's treatment group is necessary for further participant management.

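### The protocol sizes the two primary outcomes at 0.025 each but then sets every test at 5%; a stated Holm rule would settle the level and improve the chance of showing both benefits

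*Protocol article*

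**What the plan says.** Protocol article, Trial aim and hypothesis: the question is whether the product "improves joint pain and/or insulin resistance", and the hypothesis is that it is "superior to placebo in reducing patient-reported joint pain and/or improving insulin resistance". Success on one outcome is enough; success on both is the stronger form of the same claim.

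Protocol article, Statistical methods, first paragraph: the trial is to enrol 150 people, 75 in each arm, with a tenth assumed lost. The overall two-sided level is 5%, and the calculation is done "with the Bonferroni correction (α = 0.025 for each outcome". The target is a power of 90%, and the difference to be found is worded as "to detect a standardized effect size of 0.625 on either of the two co-primary outcomes".

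Protocol article, Statistical methods, second paragraph: all statistical tests are placed at a two-sided 5% level, and an analysis plan is to be prepared in advance. The Bonferroni adjustment is not repeated there, and the primary outcomes are not excepted. The article does not say how the second primary outcome is tested once the first is significant.

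**The concern.** There are two linked issues.

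1. **Which level applies.** The 0.025 level appears only in the sample-size sentence, while the analysis paragraph gives 5% for everything. A p-value of 0.04 on a primary outcome is negative under the first statement and positive under the second. With an either-or claim on two outcomes, that difference decides whether the overall 5% level is kept.

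2. **What plain Bonferroni gives up.** If 0.025 applies to each outcome whatever the other shows, then after one success a p-value between 0.025 and 0.05 on the other is called negative. Overall 5% control does not require this. Holm tests the smaller p-value at 0.025 and, if that is significant, the other at 0.05. It rejects everything Bonferroni rejects and sometimes more. The conclusion at stake is that both joint pain and insulin resistance improve.

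**Working it through.** **Inputs from the protocol article.** 75 per arm, 1:1 allocation, 10% loss, standardized effect 0.625, overall two-sided 5%, 0.025 per outcome, target power 90%. After loss, 75 × 0.90 = 67.5 evaluable per arm; 67 is used below.

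**Assumptions not in the article.** Correlation between the two outcomes: 0 for the exact results, −0.5 to 0.8 for the range. A smaller effect of 0.5 is included as an illustration.

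**Step 1: the plan's own figure.** Normal approximation: n per arm = 2(2.2414 + 1.2816)² / 0.625² = 63.5, so 64; 64/0.90 = 71.1, so 72 per arm and 144 in total. With the t-test: 65 per arm; 65/0.90 = 72.2, so 73 per arm and 146 in total. Power with 67 evaluable per arm at 0.025 is 91.0% (t-test). The stated 90% with 150 participants is reproduced, with a small margin.

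**Step 2: family-wise error if both primary outcomes are tested at 5%.** Independent outcomes: 1 − 0.95² = 9.75%. Upper bound: 0.05 + 0.05 = 10%. With Bonferroni: 1 − 0.975² = 4.94%, at most 5%.

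**Step 3: power of a single test** (noncentral t, 132 degrees of freedom, noncentrality d × √(67/2)). Write p for power at 0.025 and q for power at 0.05.
- d = 0.625: noncentrality 3.617, p = 0.9101, q = 0.9486.
- d = 0.5: noncentrality 2.894, p = 0.7340, q = 0.8193.
- No effect: p = 0.025, q = 0.05.

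**Step 4: Bonferroni against Holm, independent outcomes.**
- Both significant, Bonferroni: p₁p₂.
- Both significant, Holm: q₁q₂ − (q₁ − p₁)(q₂ − p₂), that is, both below 0.05 and at least one below 0.025.
- Outcome 1 significant, Holm: p₁ + (q₁ − p₁)p₂.
- At least one significant, either method: 1 − (1 − p₁)(1 − p₂).

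| True effects | Both, Bonferroni | Both, Holm | At least one, either method |
|---|---|---|---|
| 0.625 and 0.625 | 0.9101² = 82.8% | 0.9486² − 0.0384² = 89.8% | 99.2% |
| 0.625 and 0.5 | 66.8% | 77.4% | 97.6% |
| 0.5 and 0.5 | 0.7340² = 53.9% | 0.8193² − 0.0853² = 66.4% | 92.9% |

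Power per outcome when both effects are 0.625: 91.0% with Bonferroni; 0.9101 + 0.0384 × 0.9101 = 94.5% with Holm.

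**Step 5: only one outcome responds.** Power for the responding outcome goes from 91.0% to 0.9101 + 0.0384 × 0.025 = 91.1%. The chance of a false positive on the other goes from 2.5% to 0.025 + 0.025 × 0.9101 = 4.8%, still within the 5% family-wise limit.

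**Step 6: other correlations.** A simulation of 2 million draws per case (normal approximation, 67.5 per arm, both effects 0.625, correlation −0.5 to 0.8) gave power for both of 83.6–88.0% with Bonferroni and 90.6–92.3% with Holm. Power for at least one was the same under both methods at each correlation (95.6–99.96%). With neither outcome responding, family-wise error was also the same under both (4.0–5.0%). With only one responding, the gain in power for it was at most about 0.2 points.

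**The case against.** The strongest reply is that nothing is wrong with Bonferroni. It is valid under any correlation, the sample size reproduces, and the trial is powered for an effect on either outcome, a criterion on which Holm and Bonferroni have identical power. Bonferroni also gives 97.5% intervals that agree with its tests, which Holm does not offer so simply. The gain needs both outcomes to respond, and the article's own Introduction reports a fucoidan trial with unchanged HOMA, although in people without diabetes. The article sets no power target for success on both. Finally, sizing at 0.025 is compatible with Holm, whose first step uses 0.025, and the analysis plan, which is not shown, may already specify it.

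Most of this stands. A reader might infer that Bonferroni throws power away for nothing. The document does not support that: no power is lost on the criterion used for sizing, and the matching intervals are a real advantage. A reader might also infer that the trial will test both primary outcomes at an unadjusted 5%. That is not established either, because the sample-size sentence states the correction and the overall 5% level.

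What remains is that the article gives two levels without saying which governs the primary tests. It has also named 0.025 for each outcome, so a change made only in the analysis plan would leave that plan at odds with the protocol on the primary test.

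**Conclusion.** The point holds as a reconciliation and an inexpensive improvement. It shows no failure of error control. The 0.025 and 5% statements need to be brought together; the literal unadjusted reading would give 9.75% family-wise error under independence and at most 10%. Holm in place of plain Bonferroni adds about 7 points to the power for showing both benefits at effects of 0.625 (83% to 90%) and about 13 points at the assumed effects of 0.5 (54% to 66%), with 67 evaluable per arm and independent outcomes. At effects of 0.625 the gain is about 4 to 7 points over the assumed correlation range. It practically vanishes if only one outcome responds. The sample size, the 0.025-based 90% power statement and power for at least one success are unaffected.

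**What to change.** In the protocol and the analysis plan, before unblinding, state that the two primary outcomes are tested by Holm's procedure: the smaller p-value at two-sided 0.025 and, if significant, the other at two-sided 0.05. Limit the general 5% sentence to all other tests. Keep 150 participants and the present power statement, which remains correct for the first step.

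The cost is one or two sentences, with no added participants or visits. If 97.5% intervals are reported, state that they need not agree with the second-step test: an outcome significant at that step with a p-value between 0.025 and 0.05 will have a 97.5% interval that includes no difference. If the trial team prefers plain Bonferroni for its matching intervals, the 5% sentence still needs an explicit exception for the primary outcomes.

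### The protocol gives two conflicting significance thresholds for the two primary outcomes: 0.025 each in the sample-size paragraph, 5% for every test in the analysis paragraph

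*Protocol article*

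**What the plan says.** The objective is an either/or claim. Under Trial aim and hypothesis, the combination is expected to be "superior to placebo in reducing patient-reported joint pain and/or improving insulin resistance".

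The first paragraph of Statistical methods sizes the trial on that basis, with a target power of 90% and a two-sided level of 5% for the trial as a whole. The target is "to detect a standardized effect size of 0.625 on either of the two co-primary outcomes". The division of the level between the two outcomes is given in the same sentence: "with the Bonferroni correction (α = 0.025 for each outcome"). The abstract repeats the overall 5% level and the success condition on either outcome, but not the 0.025.

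The second paragraph of the same section turns to the final analysis: intention to treat, no interim analyses, the software, and then the rule "All statistical tests will be two-sided at a 5% significance level". It does not set the primary outcomes apart. The paragraph on the regression model, missing data and per-protocol analysis names no significance level, no adjusted p-values and no multiplicity procedure. The protocol says that a statistical analysis plan will be written in advance; it is not at hand.

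**The concern.** The same two tests, HOMA and WOMAC pain, receive a threshold of 0.025 in one paragraph and 0.05 in the next. The success rule makes this matter. If both outcomes had to be positive, testing each at 5% would not raise the error rate of the claim. Here one positive outcome is enough, so there are two chances of a false positive, and the 0.025 is what keeps the overall level at 5%.

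The decision threshold for the primary conclusion is at stake. A p-value of, say, 0.03 on one primary outcome and a clearly null result on the other would be a positive trial under the analysis paragraph and a negative one under the sample-size paragraph. The text does not say which sentence governs, and that should not be left to be settled once results are known.

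**Working it through.** **Inputs, all from the protocol article.** Two primary outcomes; success on either; standardized effect 0.625; power 90%; 0.025 per outcome and 5% overall (Statistical methods, first paragraph); 5% for all tests (second paragraph); 75 per arm with 10% loss; 1:1 allocation; no interim analyses, so no other use of alpha. The correlation between the two test statistics is not given. Values of 0, 0.3, 0.5 and 0.8 are assumed to show the range.

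**Step 1. Reproduce the plan's own figure, to see which level it used.** Per arm, n = 2(z₁₋α/₂ + z₀.₉₀)² / 0.625².

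- At α = 0.025: 2(2.241 + 1.282)² / 0.3906 = 63.6, so 64 per arm. 64/0.90 = 71.1, so 72 per arm and 144 in total. With the t distribution it is 65 per arm, 73 after loss and 146 in total.
- At α = 0.05: 2(1.960 + 1.282)² / 0.3906 = 53.8, so 54 per arm. 54/0.90 = 60 per arm and 120 in total.

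The stated 150 fits 0.025. With 10% loss, 75 × 0.90 = 67.5 are evaluable per arm. Power per outcome at 0.025 with 67 to 68 per arm is 91.6% to 92.0% (normal approximation) or 91.0% to 91.4% (t). The stated 90% is reproduced, and 0.025 is the design level.

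**Step 2. Family-wise error under each sentence.** With both null hypotheses true and independent test statistics, the error is 1 − (1 − α)².

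- 0.05 each: 1 − 0.95² = 9.75%
- 0.025 each: 1 − 0.975² = 4.94%

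For correlated statistics it is 1 − P(|Z₁| ≤ c and |Z₂| ≤ c) under a bivariate normal, with c = 1.960 or 2.241.

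| Assumed correlation | 0.05 each | 0.025 each |
|---|---|---|
| 0 | 9.75% | 4.94% |
| 0.3 | 9.51% | 4.84% |
| 0.5 | 9.07% | 4.65% |
| 0.8 | 7.81% | 4.02% |

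Whatever the correlation, the Bonferroni bound is 5% with 0.025 each and 10% with 0.05 each.

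**Step 3. Compare with what is stated.** Testing at 0.025 delivers the overall 5% that the sample-size paragraph and the abstract announce. Testing each at 0.05 exceeds it throughout the assumed range.

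**The case against.** The best defence is that the two sentences can be reconciled. The overall level has already been set at 5% and its division between the outcomes spelled out, so the later 5% may refer to that same overall level. Bonferroni-adjusted p-values compared with 5% would satisfy both statements. A specific clause that names the outcomes and their alpha would also ordinarily take precedence over a generic line placed beside the software version. Finally, the unseen analysis plan may apply 0.025.

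Much of this stands. A reader might infer that the trial will test both primary outcomes at 5% and that its error rate therefore nearly doubles. The document does not support that as a fact: nothing withdraws the Bonferroni clause or says that the general sentence overrides it.

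The defence does not remove the conflict. The 5% sentence speaks of tests, not of a family of tests, and it covers all of them. The word overall appears one paragraph earlier, where that was meant, and is absent here. Adjusted p-values are mentioned nowhere. The Bonferroni clause appears only in the justification of the sample size, while the 5% sentence is in the paragraph on the analysis. This is also not a detail left to the analysis plan: the protocol itself states the level, in two ways, and a plan following either sentence literally would depart from the other.

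**Conclusion.** The point holds as a conflict between two current sentences on the primary decision threshold. Its direct effect is that any primary p-value between 0.025 and 0.05 has two opposite readings.

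The error inflation is conditional. It arises only if the 5% sentence is applied literally to both primary outcomes. The overall error is then 9.75% under independence, 9.5% to 9.1% at assumed correlations of 0.3 to 0.5, and 7.8% at 0.8. Calling this a near doubling of 5% is fair for zero to moderate correlation but not for high correlation.

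The sample size is not in question. The conflict should be resolved before unblinding, because it decides what counts as a positive trial.

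**What to change.** Replace the general 5% sentence in Statistical methods with:

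> Each of the two primary outcomes will be tested two-sided at 0.025 (Bonferroni, overall 5%) and reported with 97.5% confidence intervals; all other tests will be two-sided at a nominal 5% level and are supportive.

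Bonferroni is the only procedure the protocol names, so the replacement should refer to no other. The statistical analysis plan should carry the same rule; if it already does, only the protocol wording needs to be brought into line.

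The cost is one sentence. The sample size stays at 150, because it was computed at 0.025 and gives about 91% to 92% power per outcome at that level.

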### Outcome measures

The primary endpoints are change in insulin resistance, defined by the HOMA values, and patient-reported pain measured by the Western Ontario and McMaster Universities Arthritis Index (WOMAC). Secondary endpoints include anthropometry, fasting glucose and insulin, glycated hemoglobin (HbA1c), inflammatory markers (C-reactive protein, tumor necrosis factor-alpha (TNF–α), interleukin (IL)-6, IL-2, IL-8, IL-1β, IL-10 and IL-4), physical function, quality of life, pain intensity, satiety on a VAS (0 = extremely hungry, 10 = extremely full), analgesic medication use, and parameters related to COX-2 inhibition. A 7-day food record and physical activity questionnaire will be collected pre- and post-intervention to determine any changes which may have influenced observed outcomes. The trial schedule of assessments and data collection is presented in Figure 2.

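### P4 pain is collected at four visits, but the stated analysis of secondary outcomes appears to use Day 100 only; a repeated-measures model would use the Day 30 and Day 50 values at almost no cost

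*Protocol article*

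**What the plan says.** **Collection.** Under Perceived function and quality of life, the protocol article states: "Pain will also be measured on Days 0, 30, 50, and 100 using the 4-item pain intensity measure (P4". Outcome measures places this scale among the secondary endpoints ("physical function, quality of life, pain intensity, satiety on a VAS") and also lists analgesic medication use there. Permitted concomitant care has all medication use reported on the same four days.

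**Analysis.** Statistical methods begins with description: "Outcomes measured at the end of the intervention will be summarized descriptively by the treatment group, together with their baseline measures". It then gives the model: "A generalized linear regression model will be used to estimate the effect of the intervention on each outcome", and the covariates: "The model will adjust for baseline outcome value and important baseline confounders as pre-specified". No visit term, repeated-measures structure or within-person correlation is mentioned.

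**Missing data.** The two primary outcomes get multiple imputation with sensitivity analyses: "Missing data on the primary outcomes will be imputed using multiple imputations in the main ITT analysis". For the rest: "No data imputation will be considered on secondary outcomes".

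**Population.** The same section commits to intention to treat, "including all randomized participants in the group they were allocated to". Participant adherence keeps people who stop treatment in follow-up. For those who leave the study, it seeks consent to use what was collected before they left.

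**The concern.** Read together, these sentences give one end-of-treatment P4 value per participant, regressed on arm and baseline, with no provision for missing values. Anyone without a Day 100 P4 value then contributes nothing to the estimated effect on P4, whatever was recorded at Days 30 and 50.

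Two things are at stake. The first is agreement with the plan's own commitments: a complete-case comparison does not include everyone randomized, and data kept with consent after withdrawal would have no stated use. The second is bias. If people leave because their pain is not improving, and do so differently by arm, the completers are no longer comparable. The interim pain scores carry the information needed to correct for that. P4 is the only pain scale that the article's text describes as measured between baseline and Day 100, and pain is half of the trial hypothesis.

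**Working it through.** **1. The plan's own figure.** Statistical methods gives 150 participants for 90% power, a standardized effect of 0.625, α = 0.025 per co-primary outcome and 10% loss.

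- Normal approximation: n per arm = 2(z₀.₉₈₇₅ + z₀.₉₀)² / 0.625² = 2(2.241 + 1.282)² / 0.3906 ≈ 63.5, so 64. Then 64/0.9 = 71.1, so 72 per arm, or 144.
- t-test: 65 per arm. Then 65/0.9 = 72.2, so 73 per arm, or 146.

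The stated 150 is reproduced closely. This point does not depend on it.

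**2. How many are affected.** 0.10 × 150 = 15 participants without a Day 100 value at the planned loss.

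**3. Two estimators compared by simulation, 75 per arm.**

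- Complete case: Y₁₀₀ = β₀ + β₁·arm + β₂·Y₀, fitted to those with Y₁₀₀.
- With interim visits: predict missing Y₁₀₀ from arm, Y₀, Y₃₀ and Y₅₀ using the completers, then fit the same model to everyone. This stands in for the point estimate of a likelihood-based repeated-measures model.

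None of the following inputs is in the article: a true Day 100 benefit of 0.5 or 0.625 SD, inter-visit correlations of 0.5 to 0.75, and the dropout mechanism. Pain-driven loss depends on Day 50 pain. Relative error is complete-case estimate / truth − 1. A dash means that no figure was recorded.

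| Assumed loss | Missing | Truth | Complete case | With Days 30/50 | Relative error |
|---|---|---|---|---|---|
| Pain-driven, active arm only (correlation 0.5) | 10% | 0.500 | 0.546 | 0.494 | +9.2% |
| Same (correlation 0.7) | 10% | 0.500 | 0.547 | 0.502 | +9.4% |
| Pain-driven, placebo arm only, run 1 | 9% | 0.625 | 0.570 | 0.625 | −8.8% |
| Same, run 2 | 9% | 0.625 | 0.551 | 0.625 | −11.8% |
| Same, run 3 | about 10% | 0.625 | 0.552 | – | −11.7% |
| Pain-driven, same rule in both arms, run 1 | 9% | 0.625 | 0.601 | – | −3.8% |
| Same, run 2 | 9% | 0.625 | 0.611 | – | −2.2% |

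Runs of the same type differ in their assumed details.

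At about twice the planned loss, the complete-case results were:

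- Active arm only, 20% missing: 0.595 and 0.578 against 0.500.
- Placebo arm only: 0.528 at 18% missing and 0.470 at 17%, against 0.625.
- Same rule in both arms: 0.587 at 16% missing and 0.599 at 19%, against 0.625.

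**4. Random loss.** Both estimators are unbiased. The standard deviation of the estimate at 10% loss falls from 0.151 to 0.149 (correlation 0.5) or from 0.124 to 0.123 (0.7). At 20% loss it falls from 0.158 to 0.156 or from 0.131 to 0.127. These are reductions of about 1–3%.

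**The case against.** The strongest reply is that the article never says the interim values will be discarded. The end-of-intervention wording belongs to the descriptive sentence, and the model sentence names no time point. Barring imputation does not bar a likelihood-based repeated-measures model, and a statistical analysis plan not shown here may specify one. All of this stands, so it would be wrong to report discarding as a stated decision. It remains true that the model and covariates that the article does name are those of a single-time-point analysis.

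The magnitude is also open to challenge. Most of the bias comes from assuming pain-driven dropout in one arm only, which nothing in the article suggests. The planned loss is 10%, 0.625 is the target for the primary outcomes rather than for P4, and a bias of 0.055 (0.625 − 0.570) is about a third of the estimate's standard deviation of 0.151. This stands too. The direction is not reassuring, however: dropout driven by pain in the placebo arm shrinks the effect, and in the active arm it inflates it.

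Loss may also be small. Late questionnaires are followed up by telephone after 7 days, and staff chase missing items.

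A reader might go further and infer that imputation of WOMAC pain is defective because it ignores interim P4. The article does not support that. It lists no imputation variables, and choosing them is ordinary analysis-plan content. Interim P4 and medication reports would not be the only on-treatment information either, since daily adherence scans and side-effect reports are collected. The WOMAC visit days lie in a figure that is not shown.

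**Conclusion.** The point holds as a cheap improvement to the analysis of secondary outcomes. On its natural reading, the text analyses P4 and analgesic use at one time point among completers, although both are recorded at four, and this fits poorly with the intention-to-treat statement and the provision for data from before withdrawal.

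Its practical size is uncertain: nil for bias under random loss, about 2–4% at roughly 9% loss with a common pain-driven rule, and about 9–12% at 9–10% loss when that dropout is confined to one arm. Removal of the bias assumes that missingness depends only on observed data. If it depends on the unseen Day 100 pain, some bias stays. People lost before Day 30 have no interim value to contribute. The primary analyses are not called into question.

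**What to change.** In Statistical methods, or in the analysis plan before unblinding:

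- **P4:** analyse Days 30, 50 and 100 in a likelihood-based repeated-measures mixed model with baseline P4, arm, visit and arm-by-visit terms and an unstructured covariance. Report the Day 100 contrast as the result. Everyone with at least one post-baseline value then contributes.
- **Analgesic use:** use a corresponding repeated-measures model over the same visits, such as a logistic mixed model if use is recorded as yes or no.
- **Wording:** say how Days 30 and 50 enter the analysis, and state which participants each secondary analysis includes, so that the intention-to-treat sentence and the withdrawal provision agree with it. The no-imputation rule can stay as written.

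The cost is a few sentences and a few lines of SAS. No extra data, visits or participants are needed.
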